#### Economic analysis

A within-trial cost consequences analysis (CCA) will be undertaken. CCA allows consideration of a number of outcome measures alongside costs, rather than a pre-defined single outcome measure, as would be the case in a cost utility analysis using quality-adjusted life years. Base-case analysis will be conducted from the NHS perspective, with additional analyses from the societal perspective. The NHS perspective will include health service resource utilisation in terms of provider costs, commissioner costs (prices) and costs that are sometimes paid for by patients (e.g. travel). Analysis will also include data on NHS resource use for patient appointments (e.g. number of face-to-face appointments, myVideoClinic calls, telephone calls, emails) and costs of clinical tests. The societal perspective will include non-NHS costs, such as patients’ out-of-pocket expenses (e.g. travel costs, car parking, childcare costs), and wider costs such as productivity loss due to absence from work. The CCA will include a sensitivity analysis to model the cost consequences of a number of different scenarios, whereby patients take up different numbers of appointments and different proportions of patients take up myVideoClinic. Including both the NHS and societal perspectives will provide a full picture of how video clinics affect the financial burden on both the NHS and patients and may help to inform the development of new payment currencies for patient management. This is important in terms of the acceptability of myVideoClinic to the provider and commissioners because any move away from traditional face-to-face appointments risks a loss of provider income, unless locally agreed funding arrangements are implemented, which reflect the intervention’s aims to promote more efficient use of resources.

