### Recruitment and consent

Prior to each clinic where recruitment is taking place, a member of the clinical team will screen the day’s clinic list to identify eligible patients on the basis of time since transplant and age (inclusion criteria 1 and 2). Patients who meet these criteria will have the study introduced to them at the end of their routine outpatient appointment and their further eligibility assessed against inclusion criteria 3 to 7. The consultant will give eligible patients a Participant Information Sheet and those interested in study participation will have the opportunity to discuss the study with a member of the University of Birmingham research team. The research team will take written informed consent during the clinic from patients who wish to participate and the latter will complete a baseline questionnaire prior to randomisation. Patients who require more time to consider participation will be able to take the study information away and will be contacted by telephone within 7 days by a member of the research team. If a patient agrees to take part over the telephone, a consent form and baseline questionnaire will be posted to them along with a reply-paid envelope for return of the completed documents to the University of Birmingham. Once recruited, participants will stay in the study for 12 months. This will equate to between two and four follow-up appointments since the participants’ usual appointment schedule and frequency will continue to be defined by clinical need regardless of group allocation.

If a patient does not wish to participate in the study, their reason for refusal will be recorded, along with routinely collected information (age, sex and clinic attended). To further understand reasons for participants not taking part, a selection of non-participating patients (*n* = 4) will be invited to take part in a short semi-structured interview (see qualitative study section).

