#### Baseline

All patients who have consented to participate in the study will complete baseline questionnaires before being told the outcome of randomisation. Baseline questionnaires will record the following information:Sociodemographics (e.g. home postcode, sex, age, ethnicity, employment status)Clinical information (e.g. diagnosis, comorbidities, time since transplant)Current computer usagePatient satisfaction (modified VSQ-9)HRQoL (EQ-5D-5 L)Costs (e.g. healthcare use, travel and personal expenses associated with appointment attendance)

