### Sample size and study power

The sample size for the study has been determined by the effect size needed to detect a clinically significant (10 point) difference between intervention and control groups in the primary outcome measure (patient satisfaction as measured on three domains of the VSQ-9). Assuming a normal distribution of satisfaction scores, a sample size of 62 patients per group would be sufficient to detect a 10-point difference in VSQ-9 scores between groups at 80% power and an alpha of 0.05. Over a 12 month period, an estimated 267 eligible patients will be available for recruitment to the study from the four liver clinics of interest. Annually, approximately 1% of liver transplant patients at UHB undergo a re-transplant and 2% die. Thus, around 21 patients per month will be eligible for recruitment. Audit data collected from one liver clinic in early 2017 suggest that approximately 60% of eligible patients will be willing to participate in the study (13 per month). A previous randomised controlled study of video clinics in diabetes care reported an attrition rate of 30% [12]. Applying this attrition rate to our patient sample, and allowing for participant withdrawals, missing data and losses to follow-up, the required sample size for the study is 90 per group (*n* = 180 total). Recruiting at a rate of 13 patients per month, we anticipate recruitment to take approximately 14 months in total (Fig. 3).

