Secondary outcome measures will be analysed descriptively where the same data have been collected from patients in both study arms (e.g. health service use). Where secondary outcome data are relevant to the intervention group only (e.g. the incidence of technical issues during myVideoClinic appointments), these will be tabulated and basic statistical analyses performed (numbers, percentages, means/medians etc.). Attrition/withdrawal rates and rates of questionnaire completion will be analysed for both study arms and overall. Analysis of HRQoL data will follow the recommendations in the EQ-5D-5 L User Guide [34]. Health state valuations will be calculated for each profile based on pre-calculated scoring coefficients. Changes in HRQoL between baseline and study end will be assessed for each patient and both descriptive and comparative analyses will be performed to compare HRQoL between participants in the intervention and control groups.

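### Health service use, contacts and costs are headed for a descriptive comparison that gives no role to the baseline costs collected or to the 3- or 6-monthly follow-up schedule

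*Protocol article*

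**What the plan says.** All references are to the protocol article.

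- **Method for these outcomes.** Statistical analysis: "Secondary outcome measures will be analysed descriptively where the same data have been collected from patients in both study arms". Health service use is the example given there. Table 1 lists health service use, number and length of clinical contacts, and costs as secondary outcomes. The abstract also calls the statistical analysis descriptive.
- **Costs.** Economic analysis: "A within-trial cost consequences analysis (CCA) will be undertaken". That section sets out perspectives, cost items and scenario analyses. It names no covariate and does not say in so many words that arm totals will be compared unadjusted.
- **Baseline data.** The baseline questionnaire records "Costs (e.g. healthcare use, travel and personal expenses associated with appointment attendance".
- **Schedule.** Background and Follow-up describe 3-monthly and 6-monthly schedules. On visits over the 12 months, Recruitment and consent says: "This will equate to between two and four follow-up appointments". Frequency continues to follow clinical need whichever arm the patient is in.
- **Randomisation.** 1:1 with an online tool; stratification by schedule is not described.
- **Where baseline values and covariates do appear.** Health-related quality of life is assessed as change from baseline with a comparative analysis, and age is to be controlled for.

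**The concern.** The number of scheduled appointments is a main component of contacts, of NHS appointment and test costs, and of travel costs. A patient on the 3-monthly schedule is due about twice as many visits as one on the 6-monthly schedule, and the schedule in force at enrolment is known before allocation. A descriptive comparison leaves this predictable variation in the arm difference, together with any chance imbalance in schedule.

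Cost is a stated secondary aim, and the Economic analysis section expects the results to bear on payment arrangements and on acceptability to provider and commissioners. A modest saving or excess is then harder to see than it need be, although the data that would sharpen the comparison are already being collected or are known to the clinic.

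**Working it through.** **1. The plan's own sample size.** Sample size and study power states "a sample size of 62 patients per group would be sufficient to detect a 10-point difference in VSQ-9 scores between groups" (power 80%, alpha 0.05). It then allows for 30% attrition and reaches 90 per group.

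- 62 / (1 − 0.30) = 88.6, so 89 per group. The stated 90 agrees with this after rounding up.
- Completers if 30% are lost: 90 × 0.70 = 63 per arm.

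The two arm sizes used below are therefore 90 and 63.

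**2. Chance imbalance in scheduled visits.** Inputs from the article: about 2 visits a year on the 6-monthly schedule and about 4 on the 3-monthly schedule (Follow-up); 1:1 allocation. Assumptions: simple randomisation, exactly 2 or 4 visits, and a share *p* on the 3-monthly schedule, which the article does not give and which is varied from 10% to 90%.

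- Mean visits = 2 + 2*p*
- SD of visits = 2√(*p*(1 − *p*))
- SE of the arm difference = SD × √(2/*n*)
- 95% limit as a share of mean visits = 1.96 × SE / mean

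At *p* = 0.5 and *n* = 90: mean 3.0, SD 1.0, SE = √(2/90) = 0.149 visits, which is 5.0% of the mean. The 95% limit is 1.96 × 0.149 = 0.29 visits, and 0.29 / 3.0 = 9.7%.

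| Share 3-monthly | Mean visits | SD | SE, *n* = 90 | 95% limit, *n* = 90 | 95% limit, *n* = 63 |
|---|---|---|---|---|---|
| 10% | 2.2 | 0.60 | 0.089 | ±8.0% | ±9.5% |
| 30% | 2.6 | 0.92 | 0.137 | ±10.3% | ±12.3% |
| 50% | 3.0 | 1.00 | 0.149 | ±9.7% | ±11.6% |
| 70% | 3.4 | 0.92 | 0.137 | ±7.9% | ±9.4% |
| 90% | 3.8 | 0.60 | 0.089 | ±4.6% | ±5.5% |

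The typical imbalance is smaller than the limit. At *p* = 0.5 and *n* = 90 the median absolute difference is 0.6745 × 5.0% ≈ 3.4% of mean visits. In a simulation of 400,000 trials at that split, the difference reached 10% of the mean in 4.3% of trials with 90 per arm and in 9.0% with 63. Conditioning on the baseline schedule removes this component.

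**3. Baseline costs.** The article gives neither a cost SD nor a correlation between baseline and follow-up costs, so the gain cannot be computed. For illustration only, adjustment multiplies the SE by √(1 − ρ²). Assumed ρ of 0.3, 0.5 and 0.7 give 0.954, 0.866 and 0.714, which are reductions of 5%, 13% and 29%.

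**The case against.** **Silence in a condensed article.** Covariates and bootstrap intervals for a cost analysis usually sit in a statistical or health economics plan, which is not shown. This stands for the Economic analysis section: a reader might infer that costs will be compared raw, but that section does not say so. It does not dispose of the point for contacts and health service use, because the Statistical analysis section does commit to a method for them, and that method is descriptive. The same part of the article gives quality of life a change from baseline and a comparative analysis.

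**Visit numbers are not fixed.** The article gives a range of two to four visits governed by clinical need, allows a face-to-face appointment after a technical failure, and records non-attendance. The two-point distribution above is a simplification, so the figures are approximate.

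**Random error, not bias.** Frequency does not depend on arm, so randomisation leaves schedule imbalance as ordinary sampling variation. This stands in full: adjustment buys precision and does not correct a wrong estimate.

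**Baseline travel costs may predict poorly in the video arm**, because the intervention is meant to remove hospital travel. This is fair, and it is a further reason not to presume a size for the gain from baseline costs.

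**The planned scenario analysis varies appointment numbers.** It models hypothetical uptake and does not adjust the observed arm difference, so it does not meet the point.

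**Conclusion.** The point holds as an optional improvement in precision. The article commits contacts and health service use, and by its own outcome list costs, to a descriptive comparison. It gives no role to two pieces of pre-randomisation information that bear directly on those outcomes.

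The chance component that could be avoided has a 95% limit of about 5% to 10% of mean scheduled visits at 90 per arm, and about 5% to 12% at 63 completers. This rests on simple randomisation, about 2 or 4 visits per patient, and an unstated schedule split.

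A reader might infer that chance shifts the arm difference itself by 10%. The calculation does not show that: the percentage is of mean visits, it is an outer limit and not a typical shift, and it carries over to costs only as far as they follow visits. Calls, emails and productivity loss also enter the costs. Nor do the documents support a claim that the planned comparison is biased.

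**What to change.** In Statistical analysis (for contacts and health service use) and Economic analysis (for costs), state that raw arm means will be shown together with an adjusted arm difference and its confidence interval, by bootstrap for costs. The difference should come from a regression on arm, the baseline value of the same cost or use where it was collected, and the schedule in force at enrolment. Use the schedule as recorded before allocation, not the number of visits that took place, since the latter can be affected by arm. If a separate health economics plan already provides for this, align the descriptive wording with it.

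The cost is a modest amount of extra analysis and the recording of each participant's schedule at enrolment. The baseline questionnaire needs no new items.

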#### Qualitative data

All interviews will be audio-recorded, transcribed verbatim and analysed using thematic analysis. The thematic analysis will be undertaken in line with the methodology outlined by Braun and Clarke [36]; 10% of the transcripts will be independently coded by a second researcher and compared, discussed and amended prior to defining the themes. Qualitative data will be analysed as data is collected to allow emerging themes to be explored in later interviews.

### Safety

The overall clinical responsibility and welfare of patients involved in the study will remain with the consultant who is providing their care and the clinical care the patient receives will not change. Any serious adverse events or adverse events reported through myhealth@QEHB or during interviews will be reported to the clinical lead immediately by the informatics team or researcher. The clinical lead will then notify the consultant responsible for the care of the patient to ensure this is dealt with immediately.

### Data monitoring

The research team and study steering group will be accountable throughout the study to an independent monitoring group, which will meet every 6 to 9 months. The independent monitoring group members will participate in discussions regarding study progress, review an unblinded report on interim study data (e.g. recruitment rates and interim analysis results) and offer independent advice to the study team.

### Data management and participant confidentiality

All patient information will remain confidential throughout the study as required by ethical and research governance approvals. At the initial eligibility screening stage, an eligibility case report form will be completed by the patient’s consultant, which records patient initials, age and sex. Once a patient has given written consent to be involved in the study, a randomisation case report form will be completed by a member of the research team and the participant assigned a unique, anonymised identifier. Members of the research team will have access to patient-identifiable data during the study, but this will only be after participants have given consent. All electronic files will be held at the University of Birmingham on password-protected secure university servers to which only members of the research team will have access. Paper copies of research data or study documentation will be held securely in a locked archive in a locked office in a swipe-card restricted area of the University of Birmingham Institute of Applied Health Research.

## Discussion

The myVideoClinic study is patient centred and has been designed with input from patients, clinicians, researchers and IT staff. It is anticipated that myVideoClinic will utilise technology to improve patient satisfaction with their care. In addition, myVideoClinic could provide cost and time savings for patients, removing the need to travel long distances for outpatient appointments. Findings from this research could be applicable to a wide range of settings that could use video clinics. The embedded qualitative study will allow the views of patients, carers/family members and healthcare professionals on the video clinic to be explored. These findings will allow a more in-depth understanding of how the video clinic was beneficial or how it could be improved for future practice.

## Study status

Study recruitment commenced on March 12, 2018, and is anticipated to continue until May 2019.

## Abbreviations

CCA: cost consequences analysis
GP: General Practitioner
HPB: hepato-pancreato-biliary
HRQoL: health-related quality of life
QEHB: Queen Elizabeth Hospital Birmingham
UHB: University Hospitals Birmingham
VSQ-9: Visit-Specific Satisfaction Instrument
